### Secondary Outcome

Secondary outcomes include the number of WBCs, the ANC, evaluation of the Brief Fatigue Inventory—Taiwanese Version, World Health Organization Quality of Life-BREF, National Cancer Institute-Common Terminology Criteria for Adverse Events & Patient Reported Outcomes, body constitution questionnaire, and frequency of G-CSF inoculation.

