**Objective:**

This study aims to evaluate the effectiveness of Chinese herbal medicine (CHM) as a complementary treatment for neutropenia prevention and immunity modulation during chemotherapy in patients with breast cancer.

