## Introduction

Chemotherapy-induced neutropenia (CIN) is a common complication and represents the most severe hematological toxicity associated with cancer chemotherapy. This condition has several complications, including severe infections, aggressive hospital management, life-threatening morbidity, and mortality [1]. Briefly, CIN is generally characterized by a decreased absolute neutrophil count (ANC) of <2000 cells/mm^3^ in the peripheral blood and is classified into 4 grades according to the National Cancer Institute Common Toxicity Criteria. The classifications of CIN severity are as follows: (1) grade 1 with an ANC of 1500-2000 cells/mm^3^, (2) grade 2 with an ANC of 1000-1500 cells/mm^3^, (3) grade 3 with an ANC of 500-1000 cells/mm^3^, and (4) grade 4 with an ANC <500 cells/mm^3^. The current standard treatment for CIN is the use of granulocyte colony-stimulating factor (G-CSF) to attenuate white blood cell (WBC) count and ANC [2]. The use of prophylactic G-CSF also improves patients’ quality of life (QoL) [3].

Breast cancer, particularly triple-negative breast cancer (TNBC), encompasses a heterogeneous group of cancer cells, and its treatment remains challenging. In patients with neoadjuvant chemotherapy (NAC)–treated TNBC with residual disease, higher stromal tumor–infiltrating lymphocytes (sTILs) in the resected tumor conferred an improved prognosis [4]. Moreover, higher pre-NAC sTILs and elevated pre-NAC expression of cytotoxic T-cell markers and cytokines are associated with better pathological complete response and overall survival rates [5]. sTILs, with a published cutoff of 30%, are the most widely studied marker of antitumor immunity. Besides, these sTILs could be used to predict improved response to NAC and better prognosis in the context of residual disease of patients lacking pathologic complete response. However, the mechanisms underlying the immunomodulatory effects of chemotherapy on sTILs and the influence of chemotherapy on the tumor-immune microenvironment are poorly understood.

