In addition to conventional therapy, an increasing number of patients with breast cancer are seeking Chinese herbal medicine (CHM), as indicated by web-based surveys exploring the perspectives of patients with breast cancer concerning complementary and alternative medicine. CHM has been reported as one of the most common complementary treatments for patients with breast cancer, associated with a possible reduction in the risk of complications, including alopecia [11], neuropathy [12], and fatigue [13], as well as with an improvement in the overall QoL [14]. Moreover, the results based on claims data suggest that using CHM in combination with conventional therapy may improve the overall survival rate by 45% [15]. However, whether CHM as a complementary therapy can alleviate myelosuppression and neutropenia remains controversial. Previous studies have demonstrated that *shenqi fuzheng* injection [16] and *xihuang* pill or capsule [17] could regulate immunity and reduce tumor markers. Nevertheless, other placebo-controlled randomized controlled trials have stated that using CHM as a complementary therapy did not prevent myelosuppression in patients with breast cancer treated with adjuvant chemotherapy [18].

Understanding how NAC reshapes antitumor immunity, both in the tumor and peripheral compartments, is essential; however, the immunomodulatory effects of NAC are still unclear. The Chinese herbs frequently used in cancer treatment, including *huang qi, dang gui, huang qin, bai zhu*, and *nuzhenzi* (Table 1), could regulate immunity, but how they affect immune cell profiles is mainly unknown. Given that some CHM has been suggested to have immune regulatory effects, we hypothesized that CHM, as a supplementary therapy during chemotherapy, could lower the risk of neutropenia in patients with breast cancer. Accordingly, we are conducting a real-world pragmatic clinical trial to evaluate the effectiveness of CHM as a complementary treatment for neutropenia prevention and immune modulation during chemotherapy in patients with breast cancer.

**Table 1 table1:** Candidate Chinese herbal medicines in this study.

Pharmaceutical Latin	Chinese name	Applications or effects	Possible side effects
*Astragalus membranaceus*	*Huang qi*	Enhance immune system, heart function, and blood sugar control	Rash, itching, runny nose, nausea, and diarrhea

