### Chemotherapy and CHM Administration Protocol

Upon the diagnosis of breast cancer in a patient, a clinical nurse manages the case. The questionnaire and blood collection before chemotherapy are represented by visit 1 (red arrow in Figure 2). The first 4 rounds of chemotherapy will be performed every 3 weeks, and visits 2-4 will be located in the second, third, and fifth rounds, respectively, 1 day before chemotherapy treatment. The following 12 rounds of chemotherapy will be performed every week, and visits 5-8 will be located in the first, fourth, seventh, and tenth rounds, respectively, 1 day before chemotherapy treatment. The patients will be followed up within 1 month after chemotherapy (Figure 2 and Table 2). Patients receiving CHM 3 times per day started the first round of chemotherapy.

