### Primary Outcome

The primary outcome used in this study is the number of immune cells, including CD4+ and CD8+ T cells (under CD45+ and CD3+ population), CD56+ NK cells (under CD45+ population), CD19+ B cells (under CD45+ population), CD14+ monocytes (under CD45+ population), and CD11c dendritic cells (under CD45+ population), as well as PD-1 expression levels in these cells. For NK cells, the expression of NKG2D will be also confirmed. The analytic panels used are listed in Table 3.

**Table 3 table3:** Antibodies used for flow cytometry analysis^a^.

Cells or conjugate	FITC^b^	PE^c^	APC^d^	APC-Cy7^e^	PE-Cy7^f^
T cells	CD45^g^	CD4	CD8	CD3	PD-1^h^
B and NK^i^ cells	CD45	NKG2D	CD56	CD19	PD-1
Monocytes or DCs^j^	CD45	CD14	CD11c	—^k^	PD-1

^a^CD45 (304006), CD4 (317410), CD8 (301014), CD3 (344818), and CD19 (302218) were purchased from Biolegend. PD-1 (25-9969-42), CD56 (17-0567-42), NKG2D (12-5878-42), CD14 (12-0149-42), and CD11c (17-0114-82) were purchased from eBioscience.

^b^FITC: fluorescein isothiocyanate.

^c^PE: phycoerythrin.

^d^APC: allophycocyanin.

^e^APC-Cy7: allophycocyanin-cyanine 7.

^f^PE-Cy7: phycoerythrin-cyanine 7.

^g^CD: cluster of differentiation.

^h^PD-1: programmed cell death protein 1.

^i^NK: natural killer.

^j^DC: dendritic cell.

^k^Not available.

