### Conclusions

In conclusion, we have proposed an open-label, single-center, pragmatic clinical trial and a real-world study to evaluate the effectiveness and safety of CHMs for treating CIN in patients with breast cancer. Using this study platform, we will analyze the effects of CHM on the regulation of QoL by evaluating the complications of chemotherapy and immune cell profiles. The findings of this study may contribute to developing an effective intervention for chemotherapy-related neutropenia in patients with breast cancer in clinical practice.

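### The stated hypothesis and the conclusions concern neutropenia, but the primary outcome and sample size concern immune cells, and no outcome counts neutropenia

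*Protocol article*

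**What the plan says.** All references are to the protocol article.

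- **Hypothesis (Introduction):** "CHM, as a supplementary therapy during chemotherapy, could lower the risk of neutropenia in patients with breast cancer". No other hypothesis is stated.
- **Objective (Abstract):** two aims, CHM as a "complementary treatment for neutropenia prevention and immunity modulation during chemotherapy in patients with breast cancer".
- **Effectiveness measures (Study Design):** effectiveness is to be judged by white cell count, ANC and G-CSF use. Immune profiles and PD-1 are introduced afterwards as additional measurements.
- **Primary Outcome:** "The primary outcome used in this study is the number of immune cells, including CD4+ and CD8+ T cells", then NK cells, B cells, monocytes, dendritic cells and PD-1 on these cells. Table 3 has no neutrophil panel.
- **Secondary Outcome:** "Secondary outcomes include the number of WBCs, the ANC", then four questionnaires and the frequency of G-CSF, seven items in all.
- **Sample Size Estimation:** based on CD4+, effect size 0.5, power 0.80, significance level .05; 64 per group, raised to 70 for 10% dropout.
- **Definition of neutropenia (Introduction only):** "CIN is generally characterized by a decreased absolute neutrophil count (ANC) of <2000 cells/mm^3^ in the peripheral blood", with four grades by ANC.
- **Conclusions:** the Abstract looks to interventions against chemotherapy-related neutropenia. The Discussion says that the trial will "evaluate the effectiveness and safety of CHMs for treating CIN in patients with breast cancer".

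**The concern.** A primary outcome should be able to answer the main claim. Here the claim is about the risk of neutropenia, and none of the primary variables is a neutrophil measure. A difference in CD4+ or PD-1 would not show that fewer patients became neutropenic, and the absence of one would not show the reverse.

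A hypothesis about risk also needs an event to count. The article defines and grades neutropenia in its background but carries neither the threshold nor the grades into an outcome. A neutropenia conclusion would have to be drawn from ANC as one secondary item among seven, or from an event definition chosen after the data are seen. Neither route has a stated power.

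**Working it through.** **1. Aims against outcomes**

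| Place in the article | Neutropenia or neutrophils | Immune cells, PD-1 |
|---|---|---|
| Hypothesis (Introduction) | yes | no |
| Objective (Abstract) | yes | yes |
| Effectiveness measures (Study Design) | WBC, ANC, G-CSF use | added after these |
| Primary Outcome | no | yes |
| Sample Size Estimation | no | CD4+ |
| Secondary Outcome | ANC and WBC counts, G-CSF frequency; no incidence or grade | no |
| Conclusions (Abstract) | yes | no |
| Conclusions (Discussion) | yes | yes, immune profiles to be analysed |

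The measures that Study Design attaches to effectiveness are all secondary, and its additional measurements are primary. The primary matches one of the two aims.

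**2. The plan's own sample size**

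Inputs from Sample Size Estimation: d = 0.5, power 0.80, alpha .05. I take the test as two-sided, since Statistical Analysis names a two-tailed t test.

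- Two-sample t test (noncentral t): n = 63.77, so 64 per group, with power 0.801. This reproduces the stated 64.
- Dropout: 64 × 1.1 = 70.4, about the stated 70. Dividing instead gives 64 / 0.9 = 71.1, so 72. The difference of two per group does not matter here.

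The figure is right for CD4+ at d = 0.5. It says nothing about neutropenia.

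**3. What 64 per group offers for incidence of neutropenia**

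The article gives no neutropenia rate, ANC mean or ANC SD, so every rate below is an assumption. With p1 the control rate, p2 the CHM rate and p̄ their mean, two-sided alpha .05 and no confounder adjustment:

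n = [1.96·√(2p̄(1−p̄)) + 0.842·√(p1(1−p1) + p2(1−p2))]² / (p1−p2)²

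Example, 50% v 30% (p̄ = 0.40): [1.96 × 0.693 + 0.842 × 0.678]² / 0.04 = 93 per group.

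| Assumed rates | n per group, 80% power | n / 0.9 | Power with 64 per group |
|---|---|---|---|
| 50% v 40% | 388 | 432 | 0.20 |
| 50% v 35% | 170 | 189 | 0.40 |
| 50% v 30% | 93 | 104 | 0.64 |
| 50% v 25% | 58 | 65 | 0.84 |

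Smallest absolute reduction detectable with 80% power at 64 per group:

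| Assumed control rate | 30% | 40% | 50% | 60% | 70% | 80% |
|---|---|---|---|---|---|---|
| Reduction (points) | 19.7 | 22.2 | 23.8 | 24.5 | 24.2 | 22.8 |

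Over these control rates, power is about 20% to 26% for a 10-point reduction and about 62% to 82% for a 20-point reduction.

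**4. How well the scheduled ANC stands in for neutropenia**

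The administration protocol times the draws before a round: "visits 2-4 will be located in the second, third, and fifth rounds, respectively, 1 day before chemotherapy treatment"; visits 5 to 8 follow the same rule. A low point between rounds could be missed, and G-CSF can raise ANC. A scheduled ANC count is therefore an imperfect substitute for an event definition.

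**The case against.** The best defence is that the trial has two aims. Immune modulation stands beside neutropenia prevention in the objective, and the primary outcome addresses it; which aim ranks first is partly for the sponsor to choose. This stands. A reader might infer that the primary test cannot answer the trial's question at all. The documents do not support that: it fails the neutropenia hypothesis and conclusion, not the whole objective.

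Nor is the neutropenia side unmeasured. ANC and G-CSF frequency are named secondary outcomes scheduled at every treatment visit, adverse events are recorded, and the grades are given, so incidence could be derived. That also stands, and it makes the repair cheap. It does not remove the gap: no listed outcome is that incidence.

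Three further inferences should be set aside.

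- The unnamed dependent variable of the logistic regression and error control across secondary outcomes are details that an article commonly leaves to the analysis plan. They are not faults in themselves.
- The word for treatment, rather than prevention, in the Discussion's conclusion is loose editing. The objective and hypothesis speak of prevention or lower risk.
- One might argue that 64 per group already serves the neutropenia question, because d = 0.5 gives 80% power on ANC too. That is true of any variable, and the article gives nothing to make d = 0.5 plausible for ANC. A pair such as 50% v 26% likewise has no source in it.

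**Conclusion.** The concern holds as a mismatch between the hypothesis and conclusions on one side and the primary outcome and sample size on the other. The primary addresses immune modulation. The neutropenia hypothesis has no designated test, no counted event and no stated power. This follows from the article's own text and does not depend on the power arithmetic.

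The size of the power gap does depend on assumptions: control rates of 30% to 80%, a two-sided .05 test, 64 evaluable per group and no adjustment. On these, only reductions of about 20 to 25 points are detectable with 80% power.

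It might seem to follow that ANC must become the primary outcome. It need not. The study is open-label, only the statistician is described as blinded, enrolment was planned to run from 2021 to 2024, and the scheduled ANC has the timing and G-CSF limits shown above. Replacing the primary this late is a trade-off for the sponsor to weigh. Realigning outcomes would also leave untouched the confounding that comes from groups formed by patients' willingness to take CHM.

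**What to change.** Before data lock, by documented amendment to protocol and registry:

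1. Reconcile the Introduction's hypothesis, Study Design, Primary Outcome, Secondary Outcome and the Discussion's Conclusions, so that they agree on which measures carry the claim of effectiveness.
2. Name the incidence of neutropenia, by the grades in the Introduction and from the ANC already collected, as the key secondary outcome. State in advance which grades count as an event.
3. Make that incidence the dependent variable of the planned adjusted logistic model, and report the baseline-adjusted group difference in ANC alongside it.
4. State which ANC values count (scheduled draws only, or also values from the clinical record) and how G-CSF use is handled in the analysis.
5. If the immune primary is kept, limit the confirmatory conclusion in the Abstract and the Discussion to immune-cell effects. Report neutropenia results as secondary or exploratory, and say that the sample size was not set for them.

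The cost is an amendment and a more modest neutropenia claim. No new patients are needed, and the incidence can be derived from data already scheduled. Promoting ANC to primary remains an option; it would carry the further cost of a documented change of primary outcome during the study and would need its own justification of effect size.

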### Safety Assessments

All adverse events (AEs) will be recorded throughout the study. In cases where AEs are caused by chemotherapy or CHM intervention, prompt measures will be taken to address those AEs. If needed, participants will be withdrawn from the study. Continuous monitoring of the participant’s blood, liver, and kidney functions, body weight, and vital signs will be performed throughout the study. The possible side effects associated with CHM are listed in Table 1.

### Flow Cytometry Analysis

Peripheral blood (10 mL) will be collected in ethylenediaminetetraacetic acid–coated tubes and processed within 24 hours of collection. Whole blood (100 µL) will be mixed directly with the fluorescence-conjugated antibodies, including CD45, CD3, CD4, CD8, CD19, CD56, NKG2D, CD14, CD11c, and PD-1 (Table 3), protected from the light, and incubated for 20 minutes at 4 ℃. Blood cells will be washed twice with 2 mL staining buffer (phosphate buffered saline+2% fetal bovine serum), centrifuged at 300×g for 5 minutes at room temperature, and further incubated with Red Blood Cell Lysis Buffer (Thermo Fisher Scientific) for lysing the erythrocytes for 10 minutes at room temperature. This step may repeat until the red blood cell is completely lyzed. The cells will be further fixed in 2% paraformaldehyde for 10 minutes at room temperature. Subsequently, the cells will be subjected to 2 additional washes with 2 mL staining buffer and centrifuged 300×g for 5 minutes at room temperature. Then, the cells will be preserved at 4 ℃ and analyzed using flow cytometry (Lyric, BD) within 3 days.

### Statistical Analysis

All statistical analyses will be performed using the SPSS software (version 13.0; IBM Corp) or SAS software (version 9.4; SAS Institute Inc). Continuous variables will be reported as mean and SD, whereas categorical variables will be reported as frequencies and percentages. The Shapiro-Wilk test will be used to analyze the normality of baseline characteristics and outcome variables. The Mann-Whitney *U* test will be used to compare nonnormally distributed continuous data, and the 2-tailed *t* test will be used to compare normally distributed continuous data. The chi-square test will be used to compare categorical data between the groups. Both primary and secondary outcomes involve repeated measurement data. The Friedman test and repeated measures ANOVA will be used to compare the differences between every visit in each group in nonparametric and parametric data, respectively. In addition, we will use generalized estimating equations or repeated measures ANOVA to compare the differences between the 2 groups. We will evaluate the risks of each clinical characteristic by the multivariate logistic regression analysis and adjust the age and other factors or characteristics that may have bias in the analysis. We set *P*<.05 as a significant difference. All data will be recorded in a case report form.

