### Sample Size Estimation

The sample size calculation was based on the mean and SD of the amount of CD4+ between control and treatment groups based on the published literature [19]. By setting the effect size as 0.5, the sample size of each group was estimated as 64 to achieve a power of 0.80 at a significance level of .05 using G*Power software (version 3.1; Heinrich-Heine-Universität Düsseldorf). After accounting for an anticipated dropout rate of 10%, the final sample size was determined to be 70 in each group.

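### The group comparison may be run by repeated measures ANOVA, which in its classical form discards every patient with a missed visit or early withdrawal

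*Protocol article*

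**What the plan says.** The Statistical Analysis section of the protocol article notes that "Both primary and secondary outcomes involve repeated measurement data". It then gives two layers of analysis.

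- **Within each group, across visits:** "The Friedman test and repeated measures ANOVA will be used to compare the differences between every visit in each group", the first for nonparametric and the second for parametric data.
- **Between CHM and non-CHM:** "generalized estimating equations or repeated measures ANOVA to compare the differences between the 2 groups". No rule says which of the two applies. The Methods paragraph of the Abstract repeats the same open choice for white cell counts, ANC, immune cells and PD-1.

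The schedule has Visits 1 to 8 and a follow-up within a month of chemotherapy (Chemotherapy and CHM Administration Protocol; Table 2).

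Under Safety Assessments, adverse events caused by chemotherapy or CHM are to be dealt with promptly, and "If needed, participants will be withdrawn from the study". The exit described is from the study, not only from CHM.

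Under Sample Size Estimation: "After accounting for an anticipated dropout rate of 10%, the final sample size was determined to be 70 in each group".

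**The concern.** The two permitted between-group methods treat incomplete patients very differently. GEE uses each visit that was observed. Classical repeated measures ANOVA needs a full row of data and deletes the patient otherwise, so someone withdrawn after Visit 5 also loses Visits 1 to 5. On that branch the trial would discard data it had already collected.

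The patients lost need not be a random subset. Withdrawal is linked to adverse events, and toxicity is plausibly related to the counts being analysed. The groups are formed by patient choice and treatment is open-label. Events caused by CHM can occur only in the CHM group, so that group has a route to withdrawal that the other lacks. If withdrawal then differs between groups, a completers-only comparison is between two differently selected sets. Because the choice of method is open, it could also be made after the pattern of missing data is known.

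**Working it through.** **1. The plan's own sample size.** Inputs from Sample Size Estimation: standardised effect 0.5, power 0.80, significance level .05. A two-sided two-sample t test needs 63.77, so 64 per group, which matches the plan. Adding 10% gives 64 × 1.1 = 70.4, in line with the planned 70. Dividing instead, 64 / 0.9 = 71.1, gives 72, a difference too small to matter here. If 10% of 70 drop out, 70 × 0.9 = 63 remain, with t-test power 79.5%. The sample size is not in error.

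**2. What deletion of incomplete patients does to 70 per group.** Assume each patient misses each time point independently with probability m (the document gives no such rate). Complete cases = 70 × (1 − m)^K. K is 8 or 9, depending on whether all of Visit 1, Visits 2 to 8 and follow-up count; the extracted Table 2 does not settle this.

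| m per visit | K = 8 | K = 9 |
|---|---|---|
| 1% | 70 × 0.99^8 = 64.6 | 70 × 0.99^9 = 63.9 |
| 2% | 59.6 | 58.4 |
| 3% | 70 × 0.97^8 = 54.9 | 70 × 0.97^9 = 53.2 |
| 5% | 46.4 | 44.1 |

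The 10% allowance is exhausted when (1 − m)^K = 0.90, that is m = 1 − 0.90^(1/K): 1.3% for K = 8 and 1.2% for K = 9. So roughly 1% missing per visit uses it up.

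**3. Can selection of completers bias the comparison?** A simulation was run on assumed inputs: 70 per group, 9 visits, within-patient correlation 0.5, and withdrawal more likely after a low value.

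- *Same withdrawal rule in both groups, no true effect:* completers-only bias 0.00 SD.
- *Same rule, true effect 0.5 SD:* completers-only estimate 0.46 to 0.48 SD.
- *More withdrawal in one group, no true effect* (26.5% against 11.7%, and 28.4% against 13.6%): completers-only analysis shows a spurious 0.08 and 0.11 SD in favour of the group losing more patients. Simple means of all available visits, which behave like unweighted GEE, show 0.04 and 0.06 SD.

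These runs show that the mechanism exists and needs differential withdrawal. They do not estimate this trial's bias, because none of the withdrawal inputs comes from the document.

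**The case against.** The strongest reply is that GEE is named first for the group comparison, both in the Abstract and in Statistical Analysis, and keeps every visit before withdrawal. That is true, and it confines the point to the ANOVA branch. It does not remove that branch, which the text expressly allows. Some authors also use repeated measures ANOVA as a loose name for a mixed model; if that is meant here, saying so would settle the matter.

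Four stronger readings are tempting, and the document does not support them.

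- *The Friedman test decides the CHM effect.* It does not. It appears only in the sentence on visits within a group.
- *The worst-affected patients leave the comparison.* Withdrawal is only if needed, after measures to address the event, and nothing makes severe neutropenia a trigger. Neutropenia is the target condition and G-CSF use is an outcome recorded across visits, so such patients may well stay.
- *Bias reaches a third of the design effect.* Removing exactly the lowest 15% of one group and 5% of the other shifts the difference by 0.274 − 0.109 = 0.165, about 0.17 SD. That is assumed extreme truncation, well above the simulated values.
- *Power collapses.* At about 55 and 46 per group (K = 8, m = 3% and 5%), a single-visit t test has 74% and 66% power. The planned analysis uses repeated visits. For a constant 0.5 SD effect, the mean of 8 visits has variance ICC + (1 − ICC)/8. At ICC 0.5 that is 0.5625, so the effect is 0.5/0.75 = 0.67 SD and power is about 93% and 89%. At ICC 0.7 power is about 86% and 79%. Independent misses are also the unfavourable pattern: dropout that is purely permanent and totals 10% leaves 63 per group.

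Finally, missing-data rules and sensitivity analyses may sit in an analysis plan that is not shown. Their absence from the article is not counted against it.

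**Conclusion.** The point holds in a limited form. The article permits, without a rule for choosing, a between-group method whose classical form deletes any patient lacking one of eight or nine measurements, alongside a provision that can end a patient's participation after an adverse event. If that option is used, observed data are thrown away, and completers may be a selected set if withdrawal differs between the groups.

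The loss of patients can be illustrated only under assumed independent misses: about 64 of 70 complete at 1% per visit and about 53 to 55 at 3%. The direction and size of any bias cannot be derived from the document. GEE avoids the deletion but is not a full cure, because in its unweighted form it is in general valid only when data are missing completely at random.

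**What to change.** - **Statistical Analysis (and the Abstract, to match):** remove repeated measures ANOVA as a between-group option and name one method that uses every observed visit. A suitable choice is a likelihood-based mixed model for repeated measures with the Visit 1 value as covariate and terms for group, visit and group-by-visit. Confounders that the plan already intends to adjust for can enter the same model. Transform only those outcomes that need it.
- **Within-group tests:** state that the Friedman and ANOVA comparisons across visits are descriptive and are not the basis for claiming a CHM effect.
- **Safety Assessments:** distinguish stopping CHM from leaving the study, so that outcomes already obtained in routine care (WBC, ANC, G-CSF use) stay in the analysis where consent allows. Who stops treatment is unchanged. Reasons for withdrawal should be reported by group.

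The cost is some wording, slightly more programming and a little extra data entry. The mixed model relies on data being missing at random, which cannot be verified. Continued flow cytometry after withdrawal would be a larger commitment, since Flow Cytometry Analysis requires a dedicated 10 mL sample processed within 24 hours. The change proposed here does not depend on it.
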